### The health-related behaviour change process: from a sedentary lifestyle to regular exercise based on the HAPA model

By identifying behavioural determinants of health and well-being such as an active lifestyle, effective interventions can be developed to increase health, quality of life and longevity [29]. Furthermore, research strongly advises that the designing and planning of interventions aimed at improving physical activity and exercise should be based on behavioural modification theories and behaviour change techniques that have shown to be valid and useful [2]. It has been suggested that interventions for behavioural change should be guided by sound behavioural change theories that help in identifying and modifying the main predictors of behaviour in each of the stages of the change process [30]. This knowledge allows for linking relevant modifiable causal factors of a behaviour to appropriate techniques for behavioural modification [31], and thus for including the specific components that facilitate behavioural change in intervention efforts. A wealth of empirical evidence supports the predictive and transformational power of traditional models of health behaviour change rooted in social cognitive theory (SCT) and its core constructs [32–35]. However, these theories primarily emphasise the motivational determinants of behavioural intentions [36], giving less attention to post-intentional determinants of behaviour adoption and maintenance. Consequently, the percentage of explained behavioural outcomes is low (≤ 30% approx.) [35]. Thus, to provide more successful explanations and effective interventions for behavioural change, theories must incorporate motivational and self-regulatory factors for the short-term initiation and long-term sustainability of behavioural changes.

The Health Action Process Approach (HAPA) model developed by Schwarzer [37–42] integrates and improves on previous social-cognitive theoretical frameworks in describing, predicting and modifying health-related behaviours. It is a hybrid approach that combines the tenets of continuum and stage models of behavioural change process for optimising the explanation, prediction and modification of healthy behaviours. In addition, the HAPA model is a dual-phase model that identifies the determinants of the initiation and maintenance of health behaviour [43]. In the HAPA model, behavioural change is a process involving two main phases (as a stage-centred model) in which several social cognitive predictors exert an influence (as a variable-centred model) on progressing from one stage to the next in the adoption of a health behaviour. It was proposed to particularly address the “intention-behaviour gap” [44], which refers to the fact that forming good intentions to act does not necessarily translate into action [45]. This observation helps explain why a significant proportion of individuals who have the goal of adhering to a healthy behaviour fail to translate their intentions into adopting the desired behaviour. Thus, one of the main contributions of the HAPA model is to distinguish between two stages or phases, each comprising a set of constructs and processes that determine behavioural enactment: an initial motivational phase that leads to the creation of a behavioural intention, and a subsequent volitional phase that leads to the implementation of an actual health behaviour. Phase-specific self-efficacy beliefs, planning and action control, depending on the stage in which the individual is involved in, namely non-intention, intention, action and disengagement, determine the progression in the change process. Stages and variables should be considered to optimise the advancement in behaviour change until a regular and sustainable habit is created.

Pre-intentional, motivational factors play a significant role in shaping intention. These factors include perceived vulnerability, which refers to the awareness of a potential threat to health resulting from a current unhealthy behaviour; outcome expectations, which involve anticipating the beneficial consequences of an alternative healthier behaviour; and, most notably, perceived action self-efficacy, which is the belief in one’s own ability to initiate the healthy behaviour. Higher levels of action self-efficacy increase the likelihood of initiating the new behaviour. These motivational factors are the prerequisites for setting behavioural goals (i.e., intentions) and provide the motivational resources that ultimately translate intention into a new behaviour [39].

A major contribution of this model is its emphasis on the post-intentional phase of behavioural change, which incorporates the self-regulation elements necessary for successfully translating a proposed goal into an actual action (initiation subphase) that is sustained over time (maintenance subphase). Engaging in a sustainable healthy behaviour in daily life requires constant self-regulatory efforts that involve establishing and maintaining behavioural goals, execution planning and managing one’s behaviour [37]. Consequently, specific self-efficacy beliefs and planning as well as action control were introduced as volitional mediators in the intention-action path and the long-term adherence to action. Specifically, action planning (if–then plans, also known as implementation intentions) and coping planning (if barrier-then coping plans) constitute a prospective, preparatory self-regulatory skill involving the strategic elaboration of organised sequences of actions, detailing the performance of behaviour in anticipated facilitatory situations, or an alternative behaviour in the face of obstacles or barriers. Action planning involves creating a detailed plan that includes specific instructions on how, when, where and other relevant parameters for performing an action, while coping planning entails developing alternative plans that anticipate barriers and obstacles that may be encountered and specify strategies for overcoming them. Planning is proposed to work in conjunction with maintenance self-efficacy, which is the belief in one’s ability to sustain the intended behaviour by effectively dealing with obstacles during the behavioural maintenance phase, and recovery self-efficacy, which refers to the perceived confidence in one’s ability to recover from setbacks and maintain adherence to the new behaviour. These factors contribute to facilitating automaticity and efficacy in behavioural enactment [37, 39].

Thus, the HAPA approach provides a parsimonious yet synergistic framework that captures the main proximal factors and processes involved in the adoption and maintenance of health-related actions.

The HAPA model has been successfully applied to the adoption and maintenance of a wide range of health-related behaviours (see the meta-analysis with meta-analytic structural equation modelling by Zhang et al. [43]) including physical activity and exercise. Gholami et al. [46, 47] synthesised and meta-analysed cross-sectional, longitudinal and experimental/intervention research investigating the main associations between HAPA constructs and physical activity and exercise behaviour. The summary effect sizes generally supported the model’s predicted associations across samples. The meta-analytic study by Zhang et al. [43] has provided further support for the HAPA direct and indirect predictions in the context of physical activity and exercise. Choi et al. [48] meta-analysed cross-sectional and longitudinal studies on active behaviour (excluding experimental/intervention studies), finding a medium overall effect size (0.28) for the impact of HAPA variables on physical activity. This effect size is comparable to that of the combined influence of the main social-cognitive theory-based constructs including self-efficacy, outcome expectations, goals/intention and self-regulation [35]. It is also consistent with the average efficacy of theory-based interventions for promoting an active lifestyle [30] and the most commonly used behaviour change techniques for adopting active behaviours [49] and maintaining them over a 6 to 15 month period [50] in adult and elderly populations. The findings of all these meta-analyses generally support those of similar previous meta-analyses on the associations between social cognitive determinants including intentions, stage-specific self-efficacy beliefs, action and coping planning and active behaviour [35, 51–53]. This information serves as a basis for designing high-quality theory-guided interventions for the promotion of an active lifestyle.

The HAPA model has been tested with a wide range of populations, sociocultural backgrounds and health behaviours, and has demonstrated its universality and stability across different scenarios [37, 43, 54]. Nevertheless, the existing evidence also points to certain differences based on gender, age, type of behaviour or health status. While the model is applicable to all individuals, some findings indicate that certain adjustments could enhance its applicability and power. For instance, some evidence indicates that the HAPA model is particularly applicable to middle-aged and older adults in predicting an active lifestyle [55] and interventions tailored to specific age groups [56] are expected to be more successful than one-size-fits-all approaches. Other research indicates that adult women utilise different resources throughout the change process compared to men (e.g., higher planning, lower social support) [57–59], which could indicate that women face specific circumstances that make it more challenging to adopt a new habit and receive acceptance from their social contexts. As a result, they may be more likely to engage in less physical activity and require tailored interventions that are adapted to their particular realities, experiences, resources and opportunities. While initial meta-analytic research found minimal effects of age, gender or sample type as moderators of the associations between HAPA constructs and exercise behaviour [46], the findings also revealed high heterogeneity. More recently Choi et al. [48] reported that effect sizes for the predictions based on the HAPA tenets were larger in the healthy participants compared to patients, men compared to women and younger individuals compared to older ones. These findings are congruent with the notion that healthy people, men and younger individuals are more likely to engage in physical activity. Zhang et al. [43] concluded that the population characteristics that were found to have minimal differences did not deviate significantly from the tenets of the HAPA model. However, these findings stress the relevance of understanding the resources, opportunities and barriers involved in self-management and self-regulatory processes that some populations — such as middle-aged women who have gone through the menopause — may encounter when attempting to make behavioural changes. The authors thus recommended that interventions be tailored to the specific circumstances of the targeted individuals. All these findings stress the relevance of investigating the gender-, age- and health status-based specificity of the process of behavioural change for health-related actions and the associated factors and dynamics involved, which can inform the development of appropriate interventions [60].

Research on the applications of the HAPA model to exercise behaviour is scarce among women. The model has primarily been tested in reproductive status-related conditions such as pregnancy [61], while research focused on middle-aged women has included breast cancer survivors [62, 63]. This research has therefore been conducted in women with reproductive (e.g., premenopausal women) or health conditions (e.g., severe or chronic illness) that are physiologically, psychologically and socially unaligned with a healthy postmenopausal status. Barg et al. [64] conducted a study involving inactive and generally healthy 40–65 yr old women. The participants received an intervention with information on physical activity levels for cancer prevention, the effect of which was considered to be “negligible” (p. 4) by the authors. This study aimed to examine changes in inactive behaviour and the motivational and volitional predictors based on the HAPA model over a 12-week period. Malaijerdi et al. [65] carried out a study targeting inactive women aged 30 to 60 years, implementing a brief educational intervention consisting of three one-hour sessions focused on exercise and health to improve HAPA motivational predictors of intention (motivational phase). They assessed HAPA predictors and intention before, immediately after the intervention and one month later and compared these with a control group of similar women not receiving such an intervention. Joveini et al. [66] reported the findings of those participants who subsequently developed the intention to exercise and who received a HAPA-based intervention aimed at offering them resources for planning the new behaviour and coping efforts as well as maintenance and recovery self-efficacy (volitional phase skills). The participants were followed for three months (HAPA constructs) and six months (behaviour). Evers et al. [67, 68] conducted a study with inactive older women in their 70 s to 90 s to investigate the short-term (six weeks), medium-term (10 weeks) and long-term (20 weeks) adherence to a supervised 6-month exercise programme. The authors offered an (assisted vs. non-assisted) intervention focused on coping planning (six weeks after starting the programme) and explored HAPA volitional predictors of adherence. Although all these studies started with and followed sedentary women, some lacked controls for comparing the influences of HAPA constructs [64] and others compared subgroups of women receiving or not receiving a HAPA-based intervention [65] or the effects of HAPA-based interventions with different delivery formats [68]. Consequently, to develop effective intervention strategies for improving physical activity among women after menopause, it is necessary understand the determinants of an active lifestyle in this population.

### The AHAWOMEN project: aims and hypotheses

The Active and Healthy Ageing in Women during early postmenopause (AHAWOMEN) project focuses on the key issue of the applicability of the HAPA model to exercise behaviour in postmenopausal women. A deeper understanding of exercise determinants in this population will allow designing appropriate interventions to promote exercise, helping women to successfully navigate the process of behaviour change. The project explores the utility of the HAPA model in combination with other psychosocial and biomedical correlates of exercise in this population, while being sensitive to the unique experiences, needs and opportunities of women in their middle age. Specifically, the objective of the AHAWOMEN project is to explore the main predictors of healthy exercise in postmenopausal women including fitness, cardiometabolic health, mental well-being, health-related quality of life, menopausal factors (e.g., frequency, intensity and burden of manifestations and symptoms) and particularly the social-cognitive constructs outlined in the HAPA model at every stage of the process of behaviour change while controlling for personal conditions (e.g., age, education level, occupational status, income, marital status). The ultimate aim is to support both theory- and evidence-guided interventions for the promotion of an active lifestyle among postmenopausal women.

Consequently, the central objective of the AHAWOMEN project is to examine the applicability of the HAPA model in explaining and predicting health-related behaviours such as exercise within this population, while taking into account the women’s own personal and social conditions, experiences, resources and opportunities.

To test the HAPA tenets in middle-aged postmenopausal women while filling the abovementioned gaps in the literature, the main aim of this study is two-fold. First, we aim to explore the influence of the social-cognitive variables relevant at each stage of the process of behavioural change based on HAPA predictions, and second, to test the goodness of fit of the model for exercise behaviour among women in early postmenopause (up to ten years after menopause). Specifically, the sub-aims of the present study protocol are the following:To explore the HAPA constructs at every stage of the change process in new exercisers, that is participants adhering to exercise practice while simultaneously receiving an intervention based on the HAPA model (Intervention group). These will be compared with regularly active (active control) and non-active (sedentary control) postmenopausal women, all with different socio-demographic, personal and clinical characteristics. Consequently, this sub-aim has the following specific objectives:to determine changes in the HAPA variables in the intervention group throughout the study phases, and in this regard:H1: we hypothesise that there will be a significant improvement in both intentional-motivational and postintentional-volitional variables in the participants in the exercise programme supplemented with the HAPA intervention.to compare the intervention, sedentary and active groups across the motivational and volitional phases of the HAPA model, and in this regard:H2: we hypothesise that, at baseline, non-active women (i.e., sedentary and intervention groups) will show similar HAPA determinants of exercise intention, while the active controls will obtain more positive results in the HAPA motivational constructs, andH3: we hypothesise that, at post-intervention and subsequent follow-ups, the new exercisers and the active women will show similar HAPA self-regulatory skills of the volitional-actional stage but will differ significantly from the sedentary women.To explore whether the HAPA constructs at the different stages of the process of behavioural change — i.e., non-intention, intention, action and disengagement — and phases of the process, that is, motivational (preintention) and volitional (intention-action-adherence), predict the adoption of exercise behaviour among postmenopausal women. In this regard:H4: we hypothesise that while the HAPA model will be applicable to this population, supporting its main predictions, adjustments in the model predictions will be necessary to optimise its explanatory power, considering the experiences, resources and opportunities of middle-aged women, andH5: personal (i.e., fitness status, physical and mental health status and sociodemographic variables) and clinical factors (i.e., menopausal manifestations and menopause-related quality of life) will intersect with HAPA variables in the prediction of exercise behaviour and behaviour change, supporting the existence of phenomena that are pertinent and exclusive of middle-aged women and are grounded in their experiences, realities and needs.

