### Procedures

The study will be publicised through several channels (e.g., media advertisements, online social networks, institutional e-mailing, gynaecology outpatient clinics, women’s associations, gyms, fitness clubs, community and university exercise programmes, neighbourhood associations, other community resources, snowball sampling) to recruit a wide sample of postmenopausal women interested in participating, along with information on how to contact the researchers (an e-mail and a telephone number). Once potential participants contact the research staff, they will be required to attend an informative session where they will receive detailed information about the general goal and procedures of the study, their rights and tasks as participants and topics such as the confidentiality of their responses and the exclusive use of data for scientific purposes. During this meeting, participants will be encouraged to express any doubts or concerns and to consult with the research staff. After agreeing to continue with enrolment, participants will be asked to sign an informed consent form. A research assistant will then contact each participant to schedule two lab visits for the first assessment phase, which will include a face-to-face clinical interview, the self-report-based evaluation conducted through an online survey implemented using an open access resource such as Limesurvey (Limesurvey GmbH, Hamburg, Germany) [95] and the remaining measures that need to be completed (e.g., weight, fitness tests). Baseline measurement will be conducted with all the women to screen eligibility criteria and collect pre-intervention data.

Upon meeting the eligibility criteria, the final study sample will be allocated to an intervention group receiving the intervention (*n* = 100), a control group of sedentary women (*n* = 100) and a control group of regularly active women (*n* = 100). The non-active participants will be randomly allocated to two groups: the intervention group and the sedentary control group, making this a randomised controlled arm of the study. This random allocation will be performed by, for example, computer-generated random numbers. The sedentary control group will be considered a waiting list group. On the other hand, women who already engage in regular exercise will be assigned to the active control group. Since these women are already active, this will be a non-randomised controlled arm of the study.

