To address the first research question, exercise behaviour and HAPA constructs of the motivational and volitional phases (primary outcomes) will be compared across different phases (baseline, post-intervention and follow-ups) (H1) and between the different study groups (intervention participants, sedentary controls, active controls) (H2 and H3). Within-group and between-group analyses will be conducted using parametric (e.g., 1-way or 2-way ANOVAs, Student *t* test) or non-parametric tests (e.g., Friedman’s *χ*^*2*^ test and Wilcoxon’s *Z* pair comparisons for related samples, Kruskal–Wallis’ *H* test and Mann–Whitney’s *U* pair comparisons for independent samples). The choice of test will be determined by the compliance with parametric assumptions of normality and homoscedasticity. A calculation of the effect size will be also conducted (e.g., Cohen’s d). Covariates (e.g., age, menopausal symptom burden) will be introduced (e.g., ANCOVAs).

The second research question (H4 and H5) will be addressed using analyses of bivariate associations (e.g., Pearson *r*, Spearman *rho*), multiple linear regression analyses and multilevel clustering analyses to explore the correlates and predictors of outcome variables as well as intraindividual profiles or patterns of associations. Path analyses and analyses of indirect relationships between variables (e.g., mediation, moderation) will allow for a deep understanding of the complex associations between the study variables. Structural equation modelling will allow for testing the fit of data to the model based on HAPA predictions. Covariates will be introduced to control for their confounding effects (e.g., perceived health status). 

In addition, psychometric properties of the measures will be analysed (e.g., Cronbach’s *alpha*, intercorrelations).

A significance level of *p* < 0.05 will be established.

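### H3 predicts that new exercisers and active women will be similar, but the named tests at p < 0.05 can only look for differences and no criterion for similarity is given

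*Protocol article*

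**What the plan says.** All references are to the protocol article.

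- **Aims and hypotheses, H3.** At post-intervention and follow-ups, "the new exercisers and the active women will show similar HAPA self-regulatory skills of the volitional-actional stage", "but will differ significantly from the sedentary women". So H3 has a similarity part (intervention versus active) and a difference part (both versus sedentary).
- **Aims and hypotheses, H2.** It predicts that "at baseline, non-active women (i.e., sedentary and intervention groups) will show similar HAPA determinants of exercise intention", and that active women will score better on the motivational constructs.
- **Procedures.** "The non-active participants will be randomly allocated to two groups", intervention and sedentary control. The active group is not randomised.
- **Data management and analyses.** Exercise behaviour and the HAPA constructs are the primary outcomes, to be compared "between the different study groups (intervention participants, sedentary controls, active controls) (H2 and H3"). The named tests are "parametric (e.g., 1-way or 2-way ANOVAs, Student *t* test"), with Kruskal–Wallis and Mann–Whitney as the non-parametric options. ANCOVA is named for covariates and Cohen's d as an example of an effect size. The decision level is: "A significance level of *p* < 0.05 will be established".
- **Participants and eligibility criteria.** The sample size is 80 per group for a comparison of means (alpha 0.05, beta 0.2, a moderate effect), raised to 100 for 20% dropout.

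The article contains no definition of similar, no equivalence margin and no rule based on an interval.

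**The concern.** Every test named for H3 has no difference as its null hypothesis. Rejecting that null is evidence that groups differ; failing to reject it is not evidence that they are alike. The test may fail because the groups are close, or because the data are too few or too noisy. The similarity part of H3 therefore has no stated method that could support it.

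The claim at stake is substantive. The intervention and active groups are not randomised against each other, and similarity would mean that women who have just started exercising have reached the self-regulatory skills of established exercisers. If non-significance were taken as support, thinner data would favour that conclusion.

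**Working it through.** **Inputs.** 80 completers per group, alpha 0.05, 80% power and 20% dropout come from the section Participants and eligibility criteria. No means, SD or standardised effect are given, so everything below is in SD units. The article does not say whether tests are one- or two-sided; two-sided is assumed.

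**The plan's own figure.**
- Dropout: 80 / (1 − 0.20) = 100. This reproduces.
- The 80 cannot be checked exactly without means or an SD. It corresponds to d = (1.960 + 0.842) × √(2/80) = 2.802 × 0.158 = 0.44, which can fairly be called moderate.

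**Chance that a real gap is non-significant (one scale, one visit).** The standard error of a difference with n per group is √(2/n), and P(non-significant) = 1 − [Φ(d/SE − 1.96) + Φ(−d/SE − 1.96)].

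| True gap (SD) | n = 80, SE = 0.158 | n = 50 (assumed), SE = 0.200 |
|---|---|---|
| 0.2 | 76% | 83% |
| 0.3 | 53% | 68% |
| 0.44 | about 20% | about 41% |

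For example, at n = 80 and d = 0.3: 0.3/0.158 = 1.897, power = Φ(−0.063) = 47%, so 53% are missed. The 50 per group is an illustration of heavier loss, not a protocol figure.

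**Precision.** The 95% interval for the difference has a half-width of 1.96 × 0.158 = 0.31 SD at 80 per group. An observed difference of zero would still be compatible with a gap of 0.3 SD either way.

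**What an equivalence rule could deliver.** Similarity is claimed if the 90% interval lies inside ±M (two one-sided tests at 0.05 each). With a true difference of zero, power = 2Φ(M/SE − 1.645) − 1, or zero if that is negative. The article gives no margin, so a range is shown.

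| Margin M (SD) | Power at 80 per group | Completers per group for 80% power | Recruited per group, 20% dropout |
|---|---|---|---|
| 0.3 | 20% | 191 | 239 |
| 0.4 | 62% | 108 | 135 |
| 0.5 | 87% | 69 | 87 |

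If the true difference is 0.2 SD rather than zero, power at the 0.5 SD margin falls from 87% to Φ(0.3/0.158 − 1.645) = Φ(0.252) = 60%.

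**H2.** Intervention and sedentary women come from one pool split at random and are compared before treatment. A test between them checks only chance imbalance. For the informative contrast, non-active versus active, the detectable d at 80% power is 2.802 × √(1/100 + 1/100) = 0.40 with one non-active group, and 2.802 × √(1/200 + 1/100) = 0.34 with both pooled.

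**The case against.** Five points can fairly be made for the plan.

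1. **No rule is stated.** A reader might infer that a non-significant test will be read as proof of similarity. The article does not say so. It lists its tests as examples and plans an effect size. This stands as a limit on the claim: what can be said is that no criterion for similarity is given and that the named tests cannot supply one. Cohen's d without an interval or threshold does not fill the gap.
2. **The miss rates are per scale and visit.** A reader might infer that H3 would be wrongly confirmed 53% of the time. That does not follow. H3 covers several volitional constructs at several visits, and the article does not say how many must agree. With a 0.3 SD gap on all of five scales and an assumed correlation of 0.5 to 0.7 between them, all five are non-significant at one visit only about a fifth to a quarter of the time.
3. **H3 has two parts.** Low power works against the required difference from sedentary women, so it does not simply favour H3 as a whole. The similarity part alone remains exposed.
4. **H2 looks like the same error but is not.** Similarity there is expected from randomisation, so a non-significant test would lead to a true conclusion. The test is redundant, not misleading.
5. **A 0.5 SD margin is not an easy way out.** A reader might conclude from the 87% power that equivalence can be tested at no cost. That margin exceeds the roughly 0.44 SD the trial is sized to detect. It would count a 0.3 SD gap as equivalent and would declare it so about 35% of the time. The margin has to be justified on its merits.

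An unseen analysis plan might add a margin. But the article itself assigns tests to H3 and sizes the study on differences alone, so the mismatch is in the stated text.

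**Conclusion.** The concern holds for the intervention-versus-active part of H3. That prediction is one of similarity, and the tests assigned to it cannot support it. At the planned 80 completers per group, the stated miss rates of 53% (0.3 SD) and 76% (0.2 SD) apply to a single scale at a single visit. They assume two-sided tests, equal variances and no covariate adjustment.

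The severity is should-fix. The comparison is non-randomised and belongs to a sub-aim worded as exploratory. The difference part of H3, the randomised intervention-versus-sedentary contrast, H1 and the modelling for H4 and H5 are not affected. H2 deserves only a minor note.

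**What to change.** **H3, intervention versus active.** For each volitional construct, report the adjusted difference with its confidence interval, and state that non-significance will not be taken as similarity. Claim similarity only if the 90% interval lies inside a margin that is justified and fixed before the data are analysed. Otherwise, report the comparison as descriptive or inconclusive. Say openly what 80 per group can deliver at the chosen margin, since margins stricter than 0.5 SD will often be inconclusive.

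**H3, versus sedentary.** Keep the difference tests.

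**H2 (minor).** Describe intervention-versus-sedentary balance at baseline without a test. Pooling the two groups against the active women is an optional gain in precision.

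**Cost.** Some wording, one interval per construct and visit, and the work of justifying a margin. Some conclusions of similarity will become inconclusive. No extra recruitment is needed if inconclusive results are accepted. Reaching 80% equivalence power at a margin of 0.4 or 0.3 SD would take 135 or 239 women per group.
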